### Study design

Using a stepped wedge randomized controlled trial (RCT) design, we randomly assign 90 practices to one of three waves (Table 1). Waves are separated by 6 months (i.e., a new wave enters the intervention phase every 6 months), and the intervention period lasts 12 months. Data collection for the primary outcome (i.e., adoption of TBC) occurs immediately prior to the beginning of the intervention period and at 12 months. BP control (i.e., secondary outcome) is measured every six months in all clusters at every time period so that each cluster provides data points in both the control and intervention conditions.

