#### Primary outcome

To measure our primary outcome (Table 4), adoption of TBC for improving adoption of HTN strategies, we adapted two instruments: the 29-item Primary Team Dynamics Survey Measure and a subscale from the Team Process Survey Measure. The Primary Team Dynamics Survey Measure is a validated instrument designed to measure team dynamics in primary care settings [46]. The 29-item instrument examines seven factors that map to four out of five elements of TBC: clear roles, shared goals, mutual trust, and effective communication. Respondents will be asked to rate their level of agreement on a scale from 1 (*Strongly disagree*) to 5 (*Strongly agree*) to statements related to TBC. Participants also complete the 5-item monitoring progress toward goals subscale of the team process measure. Respondents rate the extent to which their team participates in activities related to goal monitoring on a scale of 1 (*Not at all*) to 5 (*To a very great extent*). Practice staff in each wave complete the TBC Assessment Tool at baseline and 12- and 18-month period (end of intervention period). Both surveys were adapted to include language specifically related to HTN management. This allows us to measure the degree to which practice teams adopt TBC strategies for HTN management.

**Table 4 Tab4:** Measures and data source

	MEASURES	DATA SOURCE/COLLECTION
Primary Outcome	Adoption of team-based care for improving adoption of hypertension strategies (TBC) [46]	Provider and staff survey Baseline & 12 months
Secondary Outcomes:	Clinical outcome: BP control defined as proportion of patients with HTN who achieve BP < 140/90 (NCQA HEDIS)	EHR every 6 months for 12 months
Implementations outcomes	Fidelity: Practice facilitation [47]	Salesforce tracking system PF interviews
	Sustainability of TBC for implementing HTN management strategies and BP outcome	Provider and staff survey at 18 months EHR data at 18 months
Practice Context	Organizational readiness [39] Barriers and facilitators Staffing, financial resources Staff and provider burnout and job satisfaction	Provider and staff survey baseline and 12 months Qualitative interviews 12 months

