##### Sustainability

Sustainability of the primary (i.e., TBC principles to implement HTN strategies) and secondary outcomes (i.e., BP control) will be assessed at 18 months, six months after the intervention period ends.

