Potential moderator effects will be examined by including separately each organizational characteristic as a main effect and in interaction with the treatment condition indicator (Control vs. PF vs. Sustainability). A significant interaction effect would indicate the effect of the condition depends on the moderator, and contrasts of the control and PF periods at different levels of the moderator would be undertaken to understand the pattern of the interaction. We will conduct further analysis to explore the possibility that changes in organizational readiness mediate the effect of PF on primary and secondary outcomes. We will conduct preliminary analyses to assess whether PF (versus Control) is associated with changes at the site level. If there is a detectable effect of the PF intervention on these measures, we will assess whether the changes in these measures are associated with changes in overall average TBC and HTN management scores and changes in the rate of BP control using the Baron and Kenny “product method” as a starting point of the analysis [53]. If necessary, we will explore more complex structural equation models (SEM) adapted for Poisson outcomes [54] as well as more recently developed causal inference methods [55, 56] to evaluate the mediation.

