#### Power analysis

With the pre-specified number of sites (90) and design (Table 1; stepped-wedge design with 3 waves and 6 time periods; n = 432 TBC overall average scores), we investigated the PF intervention effect that is detectable with at least 80% power of a 2-sided significance test with α = 0.05. Power was calculated by simulating ten thousand datasets with modest correlation of TBC overall average scores over time (*r* = 0.35; ICC = 0.32) [57], and a standardized mean difference between control and PF conditions of *d* = 0.5 (i.e., a difference of half a standard deviation). Power was 0.92 to detect this effect with the planned number of sites. To allow for withdrawal of a small number of sites after baseline, we plan to enroll 90 practice sites (30 in each wave). Power for the secondary blood pressure outcome was also calculated by simulating ten thousand datasets. In all conditions, we assume an average of 150 patients with HTN per site and time period (i.e., 64,800 observations of patient BP over all sites and time periods). The intraclass correlation for BP control was specified as ICC = 0.85 based on an estimate from our previous EvidenceNOW study [25]. For the control condition, we specified a rate of BP control of 70%. For the PF condition, we specified an increase in the rate of BP control to 75%, and for the follow-up condition, we specified a decrease to 72%. The difference between the control and PF conditions corresponds to IRR = 1.07. Power to detect this IRR was > 0.99.

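### If BP readings at 24 and 30 months enter the model under the single Sustainability level, further fading biases the 18-month sustainability estimate and the PF estimate; Table 4 and the Study design section disagree on whether those readings enter

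*Protocol article*

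**What the plan says.** - **Definition of the outcome.** The Sustainability section says that sustainability of TBC and of BP control "will be assessed at 18 months, six months after the intervention period ends". Table 4 gives the BP source for this outcome as "EHR data at 18 months".
- **BP schedule, Study design section.** BP control "is measured every six months in all clusters at every time period".
- **BP schedule, Table 4.** The BP row reads "EHR every 6 months for 12 months", which stops at 12 months apart from the separate 18-month sustainability entry.
- **Timing of waves.** Waves are 6 months apart: "a new wave enters the intervention phase every 6 months), and the intervention period lasts 12 months". The Power analysis adds that there are three waves and six periods.
- **Model.** The Quantitative analysis section regresses the BP count on fixed effects for time and condition, with a log offset and a random site effect. The levels of condition are listed only in the moderator paragraph, where each moderator is entered "in interaction with the treatment condition indicator (Control vs. PF vs. Sustainability").
- **Power simulation.** It uses the same three conditions, with 70% control, 75% under PF and one later rate: "for the follow-up condition, we specified a decrease to 72" per cent.

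**The concern.** Sustainability is an 18-month quantity, but following the Study design schedule yields post-PF readings at three different distances from the end of facilitation. One Sustainability coefficient treats them as a single effect. Whether the benefit lasts once facilitators leave is the question this outcome exists to answer, and the protocol's own planning rates already assume a fall from 75% to 72%. If the decline continues, a model with one post-PF level is misspecified. The error does not stay in the sustainability estimate. It also passes through the period effects into the PF-versus-control BP contrast, which is the main result for the secondary outcome.

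**Working it through.** **1. The plan's own figures.** 72 sites x 6 periods = 432 site-periods, and 432 x 150 patients = 64,800 observations. 0.75/0.70 = 1.071, the stated IRR of 1.07. All three agree with the Power analysis.

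**2. Layout.** Table 1 is not shown, so this is inferred from the Study design and Power analysis sections (C = control; S with months since the practice's own start):

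| Wave | P1 | P2 | P3 | P4 | P5 | P6 |
|---|---|---|---|---|---|---|
| 1 | C | PF | PF | S18 | S24 | S30 |
| 2 | C | C | PF | PF | S18 | S24 |
| 3 | C | C | C | PF | PF | S18 |

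Three of the six post-PF wave-periods are not the 18-month reading. There is no control cell after P3, and in P6 every wave is post-PF.

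**3. Estimator.** For site *i* with design rows X_i (period effects, PF, S), the generalised least-squares estimate is

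b = (Σ X_i′V⁻¹X_i)⁻¹ Σ X_i′V⁻¹y_i, with V = (1 − ρ)I + ρJ.

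I took 30 sites per wave, categorical periods and ρ = 0.85, the ICC in the Power analysis, read as the correlation between a site's period-level results. The expected value of each coefficient is then a weighted sum of the true effects:

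- S coefficient: +1.46, +0.01 and −0.47 on the 18-, 24- and 30-month effects.
- PF coefficient: the PF effect itself, plus +0.35, −0.12 and −0.24 on the same three.

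The S weights sum to 1 and the PF spill-over weights to 0 (up to rounding), so a flat post-PF effect gives no bias. The negative weights arise because late fading, with no control data left, is read as a downward secular trend. Correcting for that false trend pushes the condition effects up.

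**4. Illustration in percentage points.** PF = 5 and 18-month effect = 2 come from the plan (75 − 70 and 72 − 70). The 24- and 30-month effects are assumptions; the documents give none.

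- Fade 2/1/0: S = 1.46×2 + 0.01×1 − 0.47×0 = 2.93. PF = 5 + 0.35×2 − 0.12×1 − 0.24×0 = 5.58 (5.59 unrounded).
- Fade 2/1.5/1: S = 2.92 + 0.015 − 0.47 = 2.47. PF = 5 + 0.70 − 0.18 − 0.24 = 5.28 (5.30 with unrounded weights).
- Abrupt drop 2/0/0: S = 2.92; PF = 5.71 (unrounded weights).
- Flat 2/2/2: S = 2.00; PF = 5.00.

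With linear instead of categorical time, the 2/1/0 fade gives S = 3.0 and PF = 5.8.

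**5. Check on the planned scale.** A Poisson mixed model with a log offset and random site effect, fitted to simulated counts with true rates of 70, 75 and 72/71/70%, gives a PF IRR of 1.080 against a true 1.071, and an S IRR of 1.042 against a true 1.029. The linear calculation is therefore not misleading.

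**6. Dependence on the ICC (fade 2/1/0, categorical time).**

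| ICC | S (truth 2) | PF (truth 5) |
|---|---|---|
| 0.85 | 2.93 | 5.59 |
| 0.32 | 2.48 | 5.37 |
| 0.10 | 2.06 | 5.16 |
| 0.08 | 2.01 | 5.13 |
| 0.02 | 1.82 | 5.04 |

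For the abrupt drop, S crosses its true value between ICC 0.10 (1.88) and 0.15 (2.02).

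**7. Remedies at ICC 0.85.** Splitting S into three levels, or dropping the cells after 18 months, returns exactly 2.0 and 5.0.

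**The case against.** The strongest reply is that the protocol never says a pooled coefficient will be reported as the 18-month result. The three-level indicator appears in the moderator paragraph, the main BP model does not list the levels of condition, and 72% is only a simulation input. Table 4 read literally leaves 18 months as the only post-PF BP report, in which case nothing is pooled and there is no bias. The counts do not settle the layout either: 432 is 72 × 6 on a full grid, but also 0.96 × 450, where 450 = 30 × (4 + 5 + 6) is the number of site-periods if each wave stops at its own 18-month report.

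This stands as a limit on the claim. It does not remove it, because the Study design section says every cluster at every period, which contradicts Table 4, and the only condition coding given anywhere has one post-PF level.

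A reader might also infer that any fading inflates both estimates. The documents do not support that in general: it holds at the planned ICC of 0.85, but the sustainability bias shrinks as the ICC falls and reverses near or below about 0.1.

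Finally, the size is modest. With 150 patients per site-period, 30 sites per wave and ICC 0.85, the standard errors are about 0.7 (PF) and 1.2 points (S) under binomial variance, or 1.3 and 2.1 under Poisson variance. The illustrated biases of 0.6 and 0.9 points are below one standard error in each case. That is fair, but the bias does not shrink with more data and, at the planned ICC, it favours the intervention.

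**Conclusion.** The point holds conditionally. The protocol contradicts itself on whether BP readings after 18 months exist for the analysis. If they enter under the single Sustainability level, and the effect keeps fading after 18 months, both BP estimates are biased. At ICC 0.85 the sustainability estimate is about 2.5 to 2.9 instead of 2 points, and the PF estimate about 5.3 to 5.7 instead of 5, over the assumed fades with categorical time.

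This rests on the inferred layout, on the ICC applying to site-period results, and on fade sizes that the documents do not give. It would be wrong to conclude that the planned analysis is certainly biased: with a flat effect after 18 months, or with later readings excluded, it is not. Only the secondary BP outcome is affected. The TBC survey is scheduled at baseline, 12 and 18 months, so it has no later readings to pool. The matter should be settled before analysis, but it does not threaten the primary result.

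**What to change.** 1. Reconcile the Study design section with Table 4: state whether BP reports after a practice's own 18-month point are collected and whether they enter the model.
2. In the BP models, do one of the following:
   - end each practice's series at its own 18-month report; or
   - give the 18-, 24- and 30-month readings separate condition levels, report sustainability from the 18-month level only, and treat the later levels as exploratory.
3. Use the same coding in the moderator models.

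The cost is analysis wording and some precision; no new data are needed. At ICC 0.85 with 30 sites per wave, separate levels raise the standard errors, in SD units, from 0.074 to about 0.082 for PF and from 0.121 to 0.133 for the 18-month effect (0.133/0.121 = 1.10), about 10% each. Ending the series at 18 months costs about the same. The protocol states BP power above 0.99 for the PF contrast, so the loss is affordable there.

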### Analysis

#### Quantitative analysis

The primary outcome is the overall average score on the TBC assessment tool. The secondary outcome is patient BP control. The analysis of the effect of PF on the TBC adoption outcome measure will be based on a linear mixed model. Specifically, to assess the PF intervention effect compared to usual care, we will use a model with a random site effect, and fixed effects for time and study condition. Condition will be dummy coded with the control condition as a reference category. The fixed-effects coefficient for the contrast of the PF condition with the control condition will indicate the direction and magnitude of the difference on the overall average TBC score. Inclusion of a fixed effect for time accounts for any general time trends. We also will explore whether the time coefficient should have a random effect to capture differences in time trends across practice sites. Confidence intervals (95%) will be reported to convey precision. In addition to the effects of time and condition, covariates (e.g., organizational readiness) will be considered for inclusion in the mixed-effects model to reduce the within-group variance, if the potential covariate is predictive of the outcome.

For the BP secondary outcome, a generalized linear mixed model will be used. The count of HTN patients with BP control (< 140/90) will be regressed on fixed effects for time and condition, the natural logarithm of the total number of HTN patients as an offset, and a random site effect. For the count outcome, a Poisson model will be used, but we also will consider a negative binomial mixed model if overdispersion is found. The offset term allows us to model the *rate* of BP control in each practice site and adjusts for differences in the number of HTN patients across sites. Comparisons of conditions (e.g., PF vs. control) can be converted to incidence rate ratios (IRRs) by exponentiating the appropriate fixed-effects coefficient or contrast.

Models will be fit using the *glmmTMB* package using R software [51, 52]. Each of the PF intervention effects will be tested using a two-sided level of significance α = 0.05. For the blood pressure secondary outcome, we will also conduct sub-analyses to assess outcomes by race/ethnicity.

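### Exploratory mediation is estimated only if PF detectably changes readiness, so any reported indirect effect carries a PF-to-readiness estimate selected for being large

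*Protocol article*

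**What the plan says.** The mediation plan is in the Quantitative analysis section of the protocol article. Its status is exploratory: "We will conduct further analysis to explore the possibility that changes in organizational readiness mediate the effect of PF on primary and secondary outcomes".

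It has two steps. First: "We will conduct preliminary analyses to assess whether PF (versus Control) is associated with changes at the site level". The second step, which relates changes in readiness to changes in TBC and in BP control, is conditional: "If there is a detectable effect of the PF intervention on these measures, we will assess whether the changes in these measures" go with changes in the outcomes, "using the Baron and Kenny “product method” as a starting point of the analysis". Structural equation or causal-inference methods may follow if needed.

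Table 4 (under Primary outcome) gives the readiness schedule as "Provider and staff survey baseline and 12 months". For the TBC survey, Study design says that collection "occurs immediately prior to the beginning of the intervention period and at 12 months"; the article does not say separately whether the readiness baseline is timed the same way.

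Two general statements in Quantitative analysis bear on the first step. For the TBC outcome, "we will use a model with a random site effect, and fixed effects for time and study condition". On testing, "Each of the PF intervention effects will be tested using a two-sided level of significance" of 0.05.

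**The concern.** In the product method the indirect effect is a × b, where a is the PF effect on readiness and b the association of readiness with the outcome. The same estimate of a decides whether the product is computed and then enters the product. Among trials that report an indirect effect, a has been selected for being large, so the product is biased even if both path models are correct. The bias grows as the power of the first test falls.

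That power is likely to be modest. Readiness is measured twice per practice, not in all six periods that underlie the article's power figure for TBC.

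What is at stake is the evidence on mechanism. The Conceptual framework section hypothesizes that PF works by increasing readiness, and the Discussion presents the study of mechanisms as a contribution. Under the stated rule, the trial gives either no estimate of the indirect effect or one that is too large on average.

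**Working it through.** **Check of the method against the plan's own figure.** The article states power 0.92 for TBC at d = 0.5 and ICC 0.32. I used generalized least squares for the stated mixed model (random site effect; fixed categorical time; control, PF and sustainability conditions), with total SD 1, 30 sites per wave and 6 periods. The SE of the PF effect is 0.148, and power is Φ(0.5/0.148 − 1.96) = 0.92. The figure is reproduced. The article states no power for readiness or for mediation.

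**Inputs for readiness.**
- From the document: waves 6 months apart; 12 months of PF; 30 practices per wave; readiness at baseline and 12 months.
- Assumed: baseline is each wave's own; *detectable* means two-sided p<0.05; unit SD; ICC 0.32 as for TBC; the time-adjusted model stated for TBC. True changes of 0.3, 0.5 and 0.8 SD are shown as a range; 0.5 is the article's value for TBC.

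**Schedule in calendar months.**

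| Wave | Control reading | PF reading |
|---|---|---|
| 1 | 0 | 12 |
| 2 | 6 | 18 |
| 3 | 12 | 24 |

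Month 12 is the only time with both conditions. Every other month is observed in one wave only, so with categorical time its mean is absorbed by its own time effect.

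**Standard error of a.**
- Categorical time: wave 1 against wave 3 at month 12, SE = √(1/30 + 1/30) = √(2/30) = 0.258, whatever the ICC.
- Linear time: the least-squares calculation on the same six readings gives SE = 0.243 at ICC 0.32.

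**Formulas.** With u = d/SE:
- P(condition met) = Φ(u − 1.96) + Φ(−u − 1.96)
- E(estimate | met) = d + SE × [φ(1.96 − u) − φ(1.96 + u)] / P

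Example, categorical time, d = 0.5: u = 0.5/0.2582 = 1.9365 and P = 0.491. The conditional mean is 0.5 + 0.2582 × (0.3988 − 0.0002)/0.491 = 0.710, and 0.710/0.5 = 1.42.

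| True change (SD) | Categorical: met | Estimate ÷ truth | Linear: met | Estimate ÷ truth |
|---|---|---|---|---|
| 0.3 | 21% | 2.16 | 23% | 2.05 |
| 0.5 | 49% | 1.42 | 54% | 1.36 |
| 0.8 | 87% | 1.08 | 91% | 1.06 |

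**Does the product inherit this?** I simulated 10,000 trials per setting with a = 0.5 and b = 0.3 or 0.5. With the condition, mean a × b divided by the truth was 1.42 (categorical) or 1.36 (linear). Without it, the ratio was 0.995 to 1.01. The condition left b unchanged.

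**Sensitivity at 0.5 SD.**
- ICC 0.1 to 0.7, linear time: met in 56% to 51%, ratio 1.34 to 1.39.
- 24 practices per wave (the article's 432 scores ÷ 18 wave-periods): met in 41% (categorical) or 45% (linear), ratio 1.55 or 1.48.
- An extra common survey at month 0: met in 53% to 63%, ratio 1.36 to 1.26.
- One common calendar baseline only: not estimable with categorical time; met in 25% with linear time, ratio 1.97.
- Pre-post comparison without time adjustment: met in 98%, ratio 1.01, but PF is then confounded with calendar time.

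**The case against.** **The size is conditional.** The article gives no effect size, SD, ICC, model or threshold for readiness. At 0.8 SD the inflation is only 6% to 8%, and an unadjusted pre-post test would show almost none. This stands: the direction of the bias follows from the text, but its size does not. Reading *detectable* as p<0.05 is reasonable, because PF effects are tested at that level and the Power analysis section uses the word in connection with such a test. It remains an assumption.

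**The analysis is exploratory.** This also stands. The product method is only a starting point, and no confirmatory mediation claim is planned.

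**Removing the condition hardly helps to detect mediation.** This stands too. With a = 0.5 (SE 0.258) and an assumed b = 0.4 (SE 0.1), an unconditional Monte Carlo 95% interval for the product excludes zero in about 47% of trials, against 49% that meet the condition. Where the condition fails, the interval excludes zero in only 1% to 2%. A reader who looked only at significant indirect effects would meet much the same inflation. The sparse readiness schedule is the main cause, and dropping the condition does not change it.

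**Details belong to an analysis plan not shown.** This is true of the threshold, the readiness model and the intervals, and their absence is no fault. The condition itself is a stated rule and is open to comment.

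**Conclusion.** The point holds as a low-severity fault. The stated condition uses the PF-to-readiness estimate both to decide whether to compute the indirect effect and as a factor in it, so a reported indirect effect is exaggerated on average. Under the assumptions listed, the exaggeration at a true 0.5 SD change is about 1.4-fold, with about half of trials reaching the second step. Across 0.3 to 0.8 SD it runs from about 2.2-fold to 1.06-fold.

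A reader might infer more than the document supports:
- That this trial will skip mediation half the time and overstate it by 40%. Those figures belong to one borrowed effect size under one assumed model.
- That a proportion mediated would be biased. The article does not plan to report one.
- That a skipped second step leaves nothing on mechanism. The preliminary PF-versus-control result on readiness is produced either way, and whether readers would take a skipped step as evidence against the mechanism is speculation.
- That the main results are compromised. The primary TBC and secondary BP analyses do not depend on this step.

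**What to change.** Delete the condition. For both TBC and BP control, estimate and report the PF-to-readiness path, the readiness-to-outcome path and their product, whatever the p-value of the first path. Give the product a 95% interval from a site-level bootstrap or Monte Carlo method. State that the first path is estimated with adjustment for time.

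The cost is one sentence in the plan, some extra analysis and, often, a wide interval to report. No new data are needed. The change removes the selection bias and makes the imprecision visible; it does not make the readiness comparison more precise.
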